# Low-dose aspirin and burr-hole drainage of chronic subdural hematoma: study protocol for a randomized controlled study

**DOI:** 10.1186/s13063-018-3064-y

**Published:** 2019-01-21

**Keywords:** Burr-hole drainage, acetylsalicylic acid, chronic subdural hematoma, blood thinners, neurosurgery

## Abstract

**Background:**

Low-dose acetylsalicylic acid (ASA) in patients with chronic subdural hematoma (cSDH) represents a significant neurosurgical challenge. While continuation of ASA during the perioperative phase might increase recurrence and bleeding rates, discontinuation increases the risk of thromboembolic events. The aim of this study is to compare the postoperative recurrence and cardiovascular complication rates of patients undergoing burr-hole trepanation for cSDH with and without discontinuation of ASA.

**Methods:**

In this prospective randomized, placebo-controlled, double-blinded study we include all patients undergoing burr-hole drainage of cSDH who are under ASA treatment. The patients are randomized into two groups, one receiving ASA and the other placebo perioperatively. The study primarily seeks to compare the rate of recurrent events under ASA to that under placebo treatment. Secondary objectives are thromboembolic event rate, perioperative blood loss, postoperative anemia, intra- and postoperative blood transfusion rate, and clinical outcome.

**Discussion:**

To date, there is no evidence-based consensus on how to manage patients undergoing burr-hole drainage for cSDH who are under ASA treatment. Therefore, the decision to maintain or interrupt ASA treatment is based mostly on the surgeons’ preference. A randomized placebo-controlled study for this frequent question is urgently needed in order to provide class I evidence for the best possible treatment of this large group of patients.

**Trial registration:**

ClinicalTrials.gov: NCT03120182. Initial Release: 19.04.2017. Study protocol: V2_23.02.2017

**Electronic supplementary material:**

The online version of this article (10.1186/s13063-018-3064-y) contains supplementary material, which is available to authorized users.

## Background

Acetylsalicylic acid (ASA) is a drug widely prescribed for the primary and secondary prevention of coronary artery disease [1, 2]. ASA reduces the risk of cardiovascular death or subsequent attacks in patients with previous myocardial infarction, unstable angina pectoris, stroke, or transient ischemic attacks [3, 4]. Nearly 40% of patients who undergo non-cardiac surgery worldwide have or are at risk of coronary artery disease; of these, 4% per year develop a major intraoperative cardiovascular complication, including cardiac death, non-fatal myocardial infarction and cardiac arrest [5, 6]. In-hospital mortality due to perioperative myocardial infarction ranges from 15% to 25% [6–8]. Moreover, perioperative myocardial injury (PMI) after non-cardiac surgery, defined as troponin increase of ≥ 14 ng/L, was associated with substantial short- and long-term mortality [9].

The incidence of chronic subdural hematoma (cSDH) is estimated at 1.7–18 per 100,000 people and rises to 58 per 100,000 in people above the age of 65 [10]. Due to the significantly higher prevalence among patients older than 65 years (69%), 41% of these patients are under platelet aggregation inhibitor or oral anticoagulant treatment [11]. Antiplatelet therapy in patients with cSDH presents a significant neurosurgical challenge. Although patients seem to be at greater risk for cSDH while taking these medications, it remains unclear how antiplatelet therapy affects recurrence rates [10, 12–14]. Furthermore, in balancing the increased cardiovascular risk with increasing prevalence of cSDH, a lack of guidelines and recommendations persists regarding the perioperative management of patients with antiplatelet therapy. Some retrospective studies showed a trend for higher recurrence rates when ASA is continued in the perioperative phase after burr-hole drainage, without reaching significance [15–17]. Most surgeons still prefer to discontinue and/or revert antiplatelet therapy prior to surgery since they fear the risk of recurrence or intracranial bleeding [18, 19]. Although studies evaluating the bleeding risks once ASA is continued during the perioperative period exist (e.g., POISE, PEP trial, STRATAGEM) [6, 20–22], they exclude neurosurgical patients and are therefore not relevant with regards to neurosurgical patients. The effect of continuous ASA treatment after burr-hole drainage of cSDH remains uncertain and therefore a prospective randomized study elucidating the effect of ASA continuation on the recurrence rate and of discontinuation on the thrombotic events rate is imperative.

## Methods

### Aim

The aim of this study is to undertake a randomized controlled trial on the recurrence and cardiovascular complication rates of patients undergoing burr-hole drainage of cSDH with and without discontinuation of low-dose ASA in the perioperative phase.

### Study design

This will be a prospective, randomized, placebo-controlled, double-blinded superiority trial performed at the Neurosurgical Department of the University Hospital of Basel (Fig. 1 and Additional file 1).

**Fig. 1 Fig1:**
[figure not shown]
Study flow chart

### Outcomes

#### Primary study outcome measures

The primary study outcome measure is recurrence of cSDH requiring revision surgery within 6 months.

#### Secondary study outcome measures

Secondary outcome measures include the following:Thrombotic events, namely ST-segment elevation myocardial infarction/non-ST-elevation myocardial infarction/asymptomatic PMI (defined as troponin increase of ≥ 14 ng/L compared to baseline troponin levels), cerebral stroke, peripheral arterial occlusionOther bleeding events apart from recurrent cSDH, namely acute subdural hematoma, acute epidural hematoma, intraparenchymal bleeding or subarachnoid hemorrhage managed operatively or conservativelyIntraoperative blood lossAmount of blood/fluid collected in the drainPostoperative anemia (hemoglobin < 80 mg/L)Operation time (skin-to-skin)Hospitalization timeIntra- and postoperative blood transfusion rateClinical outcome (modified Rankin scale (mRS), Glasgow Outcome Scale (GOS), Markwalder score)

### Inclusion criteria

Informed consent as documented by signaturePatients undergoing burr-hole drainage for cSDH who are under low-dose ASA treatment (Aspirin cardio^®^ 100 mg once a day)ASA users under discontinued ASA treatment (e.g., conservatively managed for a period of time and ASA was discontinued)Patients older than 18 years

### Exclusion criteria

Patients under the age of 18 yearsA recent (30 days before randomization) major cardiac event (i.e., unstable angina, myocardial infarction or coronary revascularization)A recent (30 days before randomization) active bleeding eventPatients with known bleeding disorder (e.g., hemophilia)

### Randomization

In case of emergency operation on the same day:Randomization on the first postoperative day to ASA or placebo groupIn case of operation 24 h after last ASA intake:Preoperative randomization to ASA or placebo groupIn case of elective surgery:Preoperative randomization 5 days before surgery to ASA or Placebo group

### Surgical procedure

Burr-hole drainage and insertion of a drainage tube, by creating two burr holes in the skull, opening the dura mater, and relieving the fluid pressure caused by the chronic subdural hematoma. Eventually, a subdural (under the dura mater) or a subgaleal (over the skull bone) temporary drain is placed to continue draining the remaining fluid.

### Drug used

Aspirin cardio® (ASA), 100 mg 1–0-0/d, administered for 12 days after randomization.

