#### Compliance with study intervention

During hospitalization, compliance will be monitored by study nurses. After hospital discharge, patients will be instructed to continue taking medication until the 12th postoperative day. Compliance during the ambulatory phase of the trial will be controlled by patient or caregiver interviews during the clinical follow-up after 6 weeks. The patients will be explicitly asked if they took the study medication up to the 12th postoperative day and the empty blister and the rest of the medication, if there is one, will be collected. In case of non-compliance, a note-to-file will be completed and taken into account in the final statistical evaluation.

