### Statistical analysis

#### Datasets to be analyzed, analysis populations

The full analysis set (FAS) will include all randomized patients and will be analyzed based on the intention to treat principle.

The per protocol set will include all patients of the FAS who had complete follow-up and who did not have serious protocol violations. Patients receiving the opposite treatment than that to which they were randomized will be excluded from this set.

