### Limitations

Although this is a randomized, double-blinded, placebo-controlled study, it has some limitations. Since burr-hole drainage is preformed either as an emergency or elective procedure, pre- and postoperative discontinuation time of ASA differs between the patients. By assuring that all patients under placebo will discontinue ASA at least 7 days after surgery, this bias should be minimal. Patients are often discharged before the study medication is sustained, and therefore compliance of the intake cannot be guaranteed in all patients. In order to minimize this bias, we will collect the empty medication boxes at the first follow-up visit. We expect the study to be multicentric by the first quartal of 2019, which will definitely lead to an improvement in the study quality.

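### The study-drug period is counted from randomization in one section and from surgery in another; for elective patients the two end dates lie 5 to 6 days apart

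*Protocol article*

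**What the plan says.** Protocol article, Drug used: aspirin 100 mg once a day, "administered for 12 days after randomization".

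Protocol article, Compliance with study intervention: after discharge, "patients will be instructed to continue taking medication until the 12th postoperative day". At the 6-week visit they are "explicitly asked if they took the study medication up to the 12th postoperative day", and blisters and leftover medication are collected. The section adds: "In case of non-compliance, a note-to-file will be completed and taken into account in the final statistical evaluation".

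Protocol article, Randomization (under Methods and again under Statistical consideration): there are three pathways. Same-day emergencies are randomized on the first postoperative day. Patients operated on 24 h after their last aspirin intake are randomized before surgery, on a day that is not specified. For elective surgery the rule is "Preoperative randomization 5 days before surgery to ASA or Placebo group".

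Protocol article, Limitations: the differing time off aspirin is acknowledged as a possible bias and is said to be kept small because "all patients under placebo will discontinue ASA at least 7 days after surgery".

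Protocol article, Datasets to be analyzed: the per-protocol set keeps patients "who had complete follow-up and who did not have serious protocol violations". It serves a sensitivity analysis of the primary endpoint.

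**The concern.** The two rules start the clock at different events. They agree only when randomization falls close to surgery, and the article's own scheme puts elective randomization 5 days earlier.

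Two things are at stake. The first is the exposure under test. The trial asks whether perioperative aspirin raises the rate of recurrence, and the length of postoperative aspirin or placebo is part of that question. Two readers of this article could give elective patients different postoperative courses and both be following it. Under one rule the postoperative course also differs by pathway; under the other it ends on the same day for everyone.

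The second is the standard for compliance. The interview uses the surgery-based rule only. An elective patient who was given the randomization-based course and took all of it would still have to answer no.

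**Working it through.** **The plan's own figure.** The sample size does not depend on treatment length. With assumed recurrence of 28% and 10%, two-sided alpha 0.05, power 0.80 and unpooled variance:

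n per arm = (1.960 + 0.842)² × (0.28 × 0.72 + 0.10 × 0.90) / 0.18² = 7.85 × 0.2916 / 0.0324 = 70.6, rounded up to 71, so 142 in total.

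This matches the stated 142. No duration enters, so the figure stands whichever window applies.

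**Day arithmetic.** Let surgery be day 0 and r the day of randomization.

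- Rule A (Drug used): 12 daily doses from randomization. The last dose is on day r + 11 if the first is given on the day of randomization, or r + 12 if it is given the day after.
- Rule B (Compliance): the last dose is on postoperative day 12. The number of doses is 12 − r + 1 or 12 − r, under the same two conventions.

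The values of r come from the Randomization sections: −5 for elective and +1 for same-day emergency. For the 24-hour pathway the day is not given, and −1 to 0 is assumed.

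| Pathway | r | Last dose, rule A | Last dose, rule B | Difference in end date | Total doses, A | Total doses, B |
|---|---|---|---|---|---|---|
| Elective | −5 | day 6 or 7 | day 12 | 6 or 5 days | 12 | 18 or 17 |
| Same-day emergency | +1 | day 12 or 13 | day 12 | 0 or 1 day | 12 | 12 or 11 |
| 24 h after last intake | −1 to 0 (assumed) | day 10 to 12 | day 12 | 0 to 2 days | 12 | 12 to 14 |

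Counting from the first postoperative day, an elective patient receives 6 or 7 days of study drug under rule A and 12 under rule B. The choice of first dosing day moves the result by one day, so it cannot explain a gap of 5 to 6.

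**The 7-day statement in Limitations.** This is a minimum. Rule B exceeds it in every pathway. Under rule A, suppose that usual aspirin restarts the day after study drug ends (an assumption; the article does not say). An elective placebo patient then has 7 postoperative days off aspirin if the last dose is on day 7, which just meets the minimum. If the last dose is on day 6, the patient has 6 days and misses it by one.

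**The case against.** The strongest reply has four parts.

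- **Instruction and check agree.** The patient instruction and the interview question stand in the same section and name the same day. A patient who follows that instruction passes the check. False non-compliance needs a further fact, such as a supply of 12 doses, and the article gives no blister quantity. This stands: a reader might infer that all elective patients would be misclassified, but that follows only where dosing used one rule and checking the other.
- **The per-protocol consequence is not established.** A note-to-file is not an exclusion, and nothing says that a shorter course is a serious violation. This also stands: exclusion is possible, not certain, and would touch only a sensitivity analysis.
- **The window applies to both blinded arms.** The conflict is no source of bias between arms in itself. That is correct, but the length of the contrast being compared is still undetermined for elective patients.
- **The article is a condensed text.** The schedule figure is not shown here, and the full protocol may be consistent. We therefore cannot tell whether staff work from conflicting instructions. It does not remove the conflict, because the article states both rules and reconciles them nowhere.

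A reader might also take the 7 days in Limitations as a third, competing treatment length, or as evidence for the randomization-based rule because 5 + 7 = 12. The wording supports neither. It sets a floor, which day 12 also satisfies, and it does not settle which rule was meant.

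**Conclusion.** The point holds as a contradiction in the stated intervention, confined in practice to the elective pathway: end of study drug on postoperative day 6 or 7 versus day 12. It leaves open both the postoperative exposure and the standard by which compliance is judged for these patients.

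The limits are clear. The primary analysis includes all randomized patients whichever window applies. The share of elective patients is not given, so the effect on the recurrence difference cannot be computed. The compliance consequence is conditional on mixed use of the two rules. Any effect on the per-protocol set further depends on what counts as serious, which the article does not define. The elective result rests on randomization exactly 5 days before surgery; the range for the 24-hour pathway rests on the assumed randomization day. Confidence is high for the mismatch in the text and lower for what it does to the compliance record.

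**What to change.** Reconcile Drug used with Compliance with study intervention. State one treatment window for each of the three randomization pathways, including the first dosing day and the event from which days are counted. Which window applies is for the clinical team to decide.

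Then:

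- confirm that the chosen window meets the 7-day minimum in Limitations for every pathway;
- use the same window for the quantity dispensed, the patient instructions, the interview question, the non-compliance note and the per-protocol rule;
- state whether stopping before the end of the window counts as a serious violation;
- for patients already treated, record the actual date of the last dose and judge adherence against the rule that the patient was given.

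The cost is a protocol clarification or amendment, a revised patient instruction sheet, one changed e-CRF question and, for patients already treated, retrieval of last-dose dates. The sample size does not change. It is best done before further centres join, which the article expects in early 2019, so that new sites do not read the rule differently.

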### Control intervention

The placebo therapy was administered using a compound prepared by the Hospital Pharmacy of the University Hospital of Basel packed into similarly looking blisters.

### Study measurements

#### Preoperatively/at admission

Cranial computed tomography (cCT): midline shift (MLS), hematoma width, hematoma characteristics (laminar/trabecular/septated/homogenous)Patient characteristics (age, medical history, oral anticoagulants/Clopidogrel/novel oral anticoagulants, history of falls, history of burr-hole drainage)Neurologic evaluation (NE), Glasgow Coma Scale (GCS), mRS, GOS, Markwalder score12-channel electrocardiogram (ECG)Blood pressure (BP), saturation (SAT), heart rate (HR)Laboratory tests (hemoglobin, thrombocytes, quick, international normalized ratio (INR), platelet function assay bleeding time, troponin)

#### Intraoperatively

Laboratory test 30 min to 1 h before surgery (troponin), if operation > 6 h after admissionAmount of packed red blood cells given intraoperativelyIntraoperative blood loss (in mL)

#### Postoperative Day 1

NE, GCS, mRS, GOS, Markwalder score12-channel ECGVital parameters (BP, SAT, HR) four times dailyLaboratory tests (hemoglobin, thrombocytes, quick, INR, troponin)cCT scan (MLS, hematoma width, recurrence)

#### Postoperative Day 2

NE, GCS, mRS, GOS, Markwalder score12-channel ECGVital Parameters (BP, SAT, HR) four times dailyLaboratory tests (hemoglobin, thrombocytes, quick, INR, troponin)Amount of fluid/blood collected in the drainage

#### Postoperative Day 7 or at discharge

NE, GCS, mRS, GOS, Markwalder scoreLaboratory tests (hemoglobin, thrombocytes, quick, INR, troponin)12-channel ECGVital parameters (BP, SAT, HR)Hospitalization timeAmount of packed blood cells given during hospitalization

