#### Follow-up 1 (4–6 weeks postoperatively)

NE, GCS, mRS, GOS, Markwalder scoreVital parameters (BP, SAT, HR)cCT scan (MLS, hematoma width, recurrence)

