#### Follow-up 2 (6 months postoperatively)

NE, GCS, mRS, GOS, Markwalder score (Fig. 2)

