#### Follow-up of (serious) adverse events

Patients with reported serious adverse events during hospitalization will stay in hospital until the matter is resolved. If an intracranial bleeding has been diagnosed (and in some cases operated on), patients will be followed up in our outpatient clinic. NE (GCS, GOS, mRS and Markwalder score) as well as CT scan findings will be documented at 4–6 weeks and at 6 months postoperatively. Events other than those of a neurosurgical nature (thrombotic, etc.) will be followed up in a department in our hospital (e.g., cardiology) for as long as needed.

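### Thrombotic events have no outcome window, and the components that need troponin or ECG are sought only until a last check whose timing depends on length of stay

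*Protocol article*

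**What the plan says.** The Aim section names two things to compare: recurrence and cardiovascular complications. The primary outcome has a horizon, "recurrence of cSDH requiring revision surgery within 6 months". The thrombotic outcome (infarction with or without ST elevation, asymptomatic PMI defined by a troponin rise of at least 14 ng/L over baseline, stroke, peripheral arterial occlusion) heads the secondary outcomes and has no horizon.

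Under Study measurements, troponin and ECG are listed at admission and on postoperative days 1 and 2, with a conditional troponin before surgery. They appear for the last time at "Postoperative Day 7 or at discharge". Follow-up 1 then lists "NE, GCS, mRS, GOS, Markwalder scoreVital parameters (BP, SAT, HR)cCT scan (MLS, hematoma width, recurrence" and Follow-up 2 lists "NE, GCS, mRS, GOS, Markwalder score (Fig. 2". Neither list contains a troponin, an ECG or a thrombotic-event item.

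Study drug can outlast the hospital stay. The Compliance section says "After hospital discharge, patients will be instructed to continue taking medication until the 12th postoperative day", and the Limitations section adds "Patients are often discharged before the study medication is sustained". The Drug used section gives a different end point for treatment: "administered for 12 days after randomization".

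On serious adverse events, the protocol says "Patients with reported serious adverse events during hospitalization will stay in hospital until the matter is resolved". It adds that non-neurosurgical events, thrombotic ones included, are followed up for as long as necessary. The Safety analysis section promises adverse-event summaries by type and arm but states no reporting period.

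**The concern.** The thrombotic outcome measures the price of withholding ASA, which readers will weigh against recurrence. Three features of the plan weaken that measurement.

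- Without a window, it is undefined whether an infarction in week 3 or month 4 is an outcome event.
- Asymptomatic PMI can be found only by troponin, and silent infarction only by troponin or ECG. Their detection period ends at a time that differs between patients and follows length of stay. Length of stay is itself a secondary outcome, and the serious-event rule prolongs it.
- For a symptomatic infarction or arterial occlusion after discharge, no section schedules an inquiry, although many patients are then still on study drug or placebo.

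This concerns data collection. If dates and events are not asked for at the visits, the analyst cannot recover them later.

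**Working it through.** **The plan's own figure.** The only related number is the sample size. With 28% against 10%, two-sided 5%, 80% power and unpooled variance:

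n per arm = [0.28×0.72 + 0.10×0.90] × (1.960 + 0.842)² / 0.18² = 0.2916 × 7.849 / 0.0324 = 70.6, so 71 per arm and 142 in total.

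This reproduces the stated 142 (exact power 80.2%). It concerns recurrence and is untouched by this point.

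**Inputs for the day counts.**
- Last scheduled troponin/ECG: day 7 or discharge, read here as whichever comes first.
- End of drug: postoperative day 12 (Compliance section), or 12 days from randomization (Drug used section).
- Randomization: 5 days before elective surgery; postoperative day 1 after a same-day emergency operation (Randomization section).
- Length of stay: not given, so discharge on day 3 or day 5 is assumed to show a range.

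**Reading 1: drug to postoperative day 12.** Days on drug after the last check = 12 − day of last check.

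| Last check | Days without troponin/ECG | Share of 12 |
|---|---|---|
| Day 7 | 12 − 7 = 5 | 42% |
| Day 5 (assumed discharge) | 12 − 5 = 7 | 58% |
| Day 3 (assumed discharge) | 12 − 3 = 9 | 75% |

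**Reading 2: 12 days from randomization.** The last dose falls on day r + 11 or r + 12, where r is the postoperative day of randomization and the choice depends on whether that day counts.
- Elective, r = −5: last dose on day 6 to 7. A day-7 check leaves almost no gap.
- Same-day emergency, r = 1: last dose on day 12 to 13. A day-7 check leaves 5 to 6 days.
- Patients operated on 24 h after the last ASA intake are randomized before surgery on a day that is not stated, so no figure can be given.

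The gap therefore depends on which statement of duration applies and on the route of entry.

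**Direction of the effect.** Let s be the chance that a true event is detected. If s is the same in both arms, observed difference = s × true difference. Events are lost and the absolute difference shrinks, but no arm is favored in detection. If s differs by arm, the comparison is also distorted. For the troponin/ECG components that requires the timing of the last check, hence length of stay, to differ by arm. The documents give neither a length of stay nor a thrombotic event rate for this population, so s and the number of lost events cannot be computed.

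**The case against.** **The visit lists are condensed.** The 6-week compliance interview and blister collection appear in the Compliance section but not in the Follow-up 1 list. The Follow-up 2 list has no revision-surgery item, although the primary outcome runs to 6 months. The schedule figure is not shown, and an article commonly leaves event recording to the full protocol. This stands: a reader might infer that neither visit asks about thrombotic events, but the text does not prove it. What remains is that no section schedules such an inquiry, and that the outcome definition itself lacks a window.

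**Late events are not all lost.** Neurologic evaluation at both follow-ups, and the CT at 4–6 weeks, may reveal stroke. Symptomatic infarction or arterial occlusion may arrive as adverse events. This also stands: loss is certain only for what needs troponin or ECG.

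**The serious-event rule is about hospital stay.** Its reference to hospitalization says who remains in hospital. It does not limit which events are recorded. A reader might infer that thrombosis is counted only in hospital; no section says so.

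**Bias toward stopping ASA is not shown.** Blinded randomization gives both arms the same schedule. Distortion requires length of stay to differ by arm, and if the check is due at day 7 at the latest, the difference in detection time is bounded. A difference is conceivable, because the trial itself expects more recurrence on ASA, but no figure supports treating it as fact.

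**The larger percentages are conditional.** The 42% holds only under the postoperative-day-12 reading, and the 75% adds an assumed day-3 discharge. Setting 7 days against a recurrence window of about 180 days (roughly 4%) compares scheduled cardiac tests with a clinical event that itself has no scheduled CT after 4–6 weeks. It should not be used as a measure of how much thrombosis is missed.

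**Conclusion.** The point holds in limited form. The thrombotic outcome needs a window, and detection of asymptomatic PMI and silent infarction depends on length of stay. No inquiry about later infarction or arterial occlusion is scheduled in the text available. A day-7 check leaves 5 of 12 postoperative treatment days without troponin or ECG if drug runs to postoperative day 12. With 12 days from randomization, the gap is almost nil for elective patients and about 5 to 6 days for same-day emergency patients. Earlier discharge widens these gaps by an amount the documents do not allow one to state.

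The expected consequence is fewer detected events and a diluted absolute difference. The documents support neither a claim that late thrombotic events are generally missed nor one that the trial is tilted toward stopping ASA. A secondary outcome is affected; the primary analysis and the 142 patients are not. The change should be made because it is cheap now and cannot be made after the visits have passed.

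**What to change.** 1. State one window for symptomatic thrombotic events for every patient: randomization to Follow-up 1 as the main window, with 6 months as supportive.
2. At the existing Follow-up 1 and Follow-up 2 visits, add a dated, structured question with a record check on infarction, stroke and arterial occlusion since the last contact. If the full protocol already has this, say so in the outcome definition.
3. Analyze asymptomatic PMI as a separate component over a fixed in-hospital window common to all: troponin up to postoperative day 2, counting only values after randomization. For same-day emergency patients, who are randomized on postoperative day 1, a day-1 value taken before study drug is then not counted as an event. Report the day-7-or-discharge value separately.
4. State the adverse-event reporting period in its own sentence and leave the hospital-stay rule for serious events unchanged.
5. Reconcile the two statements of how long study drug is given.

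The cost is a few e-CRF fields and several sentences, with no new visit. There is slightly more data entry, some late events will rest on patient or record report, and PMI appearing after day 2 falls outside the main PMI comparison.
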